### 2.10. Protocol Modifications

During the conduction of the trial, if we observe a higher-than-expected drop-out rate at the two-weeks post-abortion follow-up, we will increase the sample size from 90 (calculated on a 20% attrition rate) to 110 (calculated on a 35% attrition rate) to achieve precision for the estimation of the effect size. Paper-based questionnaires will be left for women to fill out on their own. However, if participants express being overwhelmed by the amount of information required, we will conduct an interview during which participants could ask clarifying questions. This approach will minimize missing data and enhance the retention rate.

## 3. Discussion

We propose a two-armed randomized trial among Chinese women undergoing abortion, to assess the feasibility, acceptability, and potential effects of the START intervention. To our knowledge, this study will be the first trial to address Chinese abortion patients’ psychological wellbeing by providing a comprehensive supportive intervention based on the Transactional Model of Stress and Coping [19]. This innovative intervention contains different active components that will be delivered using different methods. Findings from this trial will allow us to evaluate the feasibility and acceptability of the intervention, which will inform intervention refinement [17]. The findings will also help to identify potential barriers and facilitators for implementing the intervention in the Chinese context [43]. As the preliminary effectiveness and effect of the intervention will also be described, the study could have important implications for relevant policymakers, practitioners, researchers, or other stakeholders [44].

We are employing a rigorous study design to ensure the internal and external validity of findings. This trial responds to the call for well-designed, rigorously conducted scientific research in abortion care in developing countries [1]. Randomization and statistical analysis adjusted for any difference in baseline characteristics between groups will protect against selection bias, and ultimately warrant internal validity [45]. The study will be performed under real-world clinical practice conditions, which will enhance the external validity and generalizability of results. All instruments used in this study have been validated in the Chinese population, which will also enhance the reliability of findings.

A further strength is that we have adopted a series of appropriate guidelines to ensure the normalization, transparency, and replication of the study. The TIDieR checklist has been used to describe the intervention [23]. Application of the CONSORT statements [20,21] and the SPIRIT 2013 Checklist [22] have been followed.

Limitations, however, need to be considered. The emotional period between a woman’s initial appointment with the clinic and 6 weeks post-abortion [46], as well as the sensitive nature of the topic, could challenge women’s adherence and completion of the study. Strategies such as keeping information simple, offering the intervention in confidential formats, and repeated reminders that are known to be effective in improving intervention adherence will be employed [47]. Another challenge lies in the uncertainties of the COVID-19 pandemic. We will follow and document all local, national, and international measures that may impact our study progress. The actual delivery of the intervention and identified barriers and facilitators of implementing the intervention will be well-recorded to inform future studies.

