## 2. Materials and Methods

The study adopts a two-arm randomized controlled trial design with quantitative and qualitative information collected. Participants will be randomly allocated to receive either the START intervention in addition to standard abortion care or standard abortion care only with a 1:1 allocation rate. The study design is directed by the CONSORT statement and its extensions [20,21] and the Standard Protocol Items: Recommendations for Interventional Trials (SPIRIT) 2013 guideline for protocols of randomized trials [22]. The research activities inconsistent with the real-world clinical practice are outlined in Figure 2.

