### 2.5. Sample Size

A formal sample-size calculation is not necessary for research objectives 1 and 2 [20]. For objective 3, G*Power software was used to determine reasonable sample size for the estimation of differences between intervention and control groups. The effect size on depression reported by similar interventions ranged from 0.39 to 1.06 [37,38,39]. G*power indicated a total of 72 participants will be required to detect a 0.39 effect size for depression, two tailed, with alpha at 0.05 and power at 90%. Anticipating a 20% attrition rate, recruitment was set at 90 (45 women per group).

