### 2.9. Data Analysis

Participant characteristics, feasibility outcomes, and quantitative acceptability outcome data will be summarized with descriptive statistics, including frequency counts and percentages (categorical variables) and mean with 95% confidence intervals (CIs) or standard deviation (continuous variables). Intervention feasibility and acceptability will be assessed against the following criteria: eligibility: ≥60% of patients screened will be eligible; recruitment: ≥80% of eligible participants will agree to participate; protocol fidelity: ≥90% of patients randomized to each group will receive the allocated intervention; retention: <20% of patients will be lost at 6 weeks after abortion; and missing data: <20% of data will be missing. Between-group differences of participant characteristics, baseline data, and effectiveness outcomes will be detected using Statistical Package for the Social Sciences (SPSS)^®^ version 23 [41]. Specifically, Chi square tests will be used for categorical/dichotomous variables, and *t*-tests or Mann–Whitney U tests for continuous variables (depending on normality). To capture changes in the effect outcomes over time, a general linear regression analysis will be performed. See Table 3 for the specific analysis approaches.

For qualitative data, audiotapes of telephone interviews will be transcribed and de-identified by the primary researcher. Transcripts and notes will be analyzed using the deductive approach of content analysis [42]. First, a structured analysis matrix will be developed based on the aims of the study and the TFA of Health Care Intervention. Then the primary researcher and nurse coordinator will independently review all de-identified data, and content fit the matrix. They will work together to group similar content within the matrix boundaries as categories, and then main categories. After abstraction of each category, the primary researcher and nurse coordinator will make a joint decision on how to model and report the results. Any discrepancies along the process will be discussed with a third reviewer until an agreement is reached. To preserve the original meaning of women’s statements, the data analysis process will be conducted using Chinese. Development of the analysis matrix and reporting process will use Chinese and English to reduce potential bias and build a shared vision among the research team.

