	Identify and deal with a dangerous relationship	Signals of unhealthy relationships Options for women experiencing an unhealthy/dangerous relationship Recognising Intimate Partner Violence (IPV) Options for women experiencing IPV
	About sex	Consent and your legal position Options for women who are forced to engage in a sexual activity
Available Coping Resources	Coping with abortion experience	Suggestions from experts (Chinese Health & Medical Development Foundation) Suggestions from women who have experienced an abortion
	Taking care your emotions	Talk to someone you trust: Tips on finding a reliable person to talk to (Marie Stopes China) Medication: free medication; Apps recommendation e.g., Tide Reading: e.g., Trauma and Recovery by Judith Herman _Chinese version Post-abortion counsellor
	Cope with IPV or sexual violence experience	Free social support services e.g., Beijing Women’s Federation hotline; The Maple Women’s Psychological Counselling Center hotlines etc. Self-help guides e.g., Guidelines for dealing with sexual assault (Marie Stopes China); SARSAS Suggestions from police Stories from IPV survivors

Abbreviations: ID: identification; IPV: intimate partner violence; Q&A: questions and answers; SARSAS: Self-help guide to rape and sexual abuse—Chinese version.

**Table 3 ijerph-19-06611-t003:** Data collection schedule and analysis method.

Concept (What)	Time (When)	Method (Who, Where, and How)	Measure (by What)	Method of Analysis
**Participant characteristics**	T-0	Primary researcher, at the clinic, face to face	Self-design questionnaire on sociodemographic characteristics, health history, and current gestation	Descriptive statistics X^2^ test comparing differences between groups of categorical/dichotomous variables *t*-test/Mann–Whitney U test comparing differences between groups of continuous variables

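### Adjustment is tied to baseline differences seen after randomisation: imbalances up to about 0.42 SD would pass as balance, and precision is lost compared with covariates fixed in advance

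*Protocol article*

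**What the plan says.** Section 2.9 (Data Analysis) puts baseline and outcome comparisons under one testing rule: "Between-group differences of participant characteristics, baseline data, and effectiveness outcomes will be detected using Statistical Package for the Social Sciences". It names chi-square tests for categorical variables and t or Mann–Whitney tests for continuous ones.

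The participant-characteristics row of Table 3 repeats this for data collected at T-0, with a chi-square test "comparing differences between groups of categorical/dichotomous variables" and a t or Mann–Whitney test for continuous variables.

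The Discussion (section 3) credits randomisation and "statistical analysis adjusted for any difference in baseline characteristics between groups will protect against selection bias", and says that the two together secure internal validity.

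For the effectiveness outcomes, Table 3 lists t or Mann–Whitney tests and, for depression, perceived support and intimate relationship, a linear regression of change over time. Section 2.9 mentions the same regression. Neither place names a baseline covariate.

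**The concern.** Read together, these sections suggest a sequence: test the baseline variables, then adjust for those that differ. Three things are wrong with that.

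- **The tests do not answer a useful question.** If randomisation was carried out properly, the null hypothesis of every baseline test is true by design, so a significant result is a chance finding. The bias in a particular trial depends on how prognostic a variable is and on how large its observed imbalance is. A p-value does not measure that product.
- **The covariates follow from the data.** A strongly prognostic variable with a moderate imbalance is left out, while an irrelevant one with a chance difference is brought in.
- **The stated benefit is misattributed.** Selection bias at allocation is prevented by an unpredictable sequence and concealed assignment (section 2.7). Adjusting for observed differences serves another purpose: it removes chance imbalance and improves precision.

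At stake is the precision of the efficacy estimates in a small trial whose results are meant to inform a larger one. The Discussion also describes an adjustment that appears nowhere in the listed analyses.

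**Working it through.** **Inputs from the article**

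- Sample size (section 2.5): "a total of 72 participants will be required", which is 72/2 = 36 per arm at 1:1 allocation.
- Recruitment (section 2.5): "Anticipating a 20% attrition rate, recruitment was set at 90 (45 women per group"). This reproduces: 72/(1 − 0.20) = 90, or 45 per arm.
- Significance level: section 2.5 gives a two-tailed alpha of 0.05 for the sample size. None is given for the baseline tests, so the same level is assumed.
- Timing (section 2.8): T-0 comes before randomisation. All randomised women should have baseline data, so 45 per arm is the main case; 36 applies to a completers-only comparison.

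The article states no operating figure for the baseline tests, so there is none to reproduce. Whether 72 follows from an effect size of 0.39 is a separate question and is not used here.

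**Step 1: the largest imbalance that passes as non-significant**

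For a two-sample t-test with n per arm, the observed standardised difference just at p = 0.05 is t(0.975; 2n − 2) × √(2/n).

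- n = 45: 1.987 × √(2/45) = 1.987 × 0.211 = 0.42 SD
- n = 36: 1.994 × √(2/36) = 1.994 × 0.236 = 0.47 SD

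**Step 2: what such an imbalance does to the outcome comparison**

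The shift is correlation × imbalance. Assume a baseline–outcome correlation of 0.6.

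- At the edge of significance: 0.6 × 0.42 = 0.25 SD, and 0.6 × 0.47 = 0.28 SD. The effect size in section 2.5 is 0.39.
- For a typical chance imbalance (one standard error) at 45 per arm: 0.6 × 0.21 = 0.13 SD.

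**Step 3: the inferred rule against a fixed covariate**

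Trials were simulated with one normally distributed baseline covariate, under two rules: (a) ANCOVA only if the baseline test gives p < 0.05, otherwise a plain t-test; (b) ANCOVA always. The correlations and the 0.5-SD effect are assumptions.

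| Power at a 0.5-SD effect | Correlation 0.5 | 0.6 | 0.7 |
|---|---|---|---|
| 36 per arm, rule (a) | 56% | 56–57% | 57% |
| 36 per arm, rule (b) | 67% | 74% | 83% |
| 45 per arm, rule (a) | 66% | 66% | 66–67% |
| 45 per arm, rule (b) | 76–77% | 83% | 90–91% |

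At correlation 0.3 and 36 per arm, rule (a) gives about 55% and rule (b) about 58%.

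Hand check of rule (b): adjustment turns the effect into 0.5/√(1 − r²), which is 0.577, 0.625 and 0.700 for r = 0.5, 0.6 and 0.7. Normal-approximation power is Φ(effect × √(n/2) − 1.96).

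- n = 36: Φ(0.49) = 69%, Φ(0.69) = 76%, Φ(1.01) = 84%
- n = 45: Φ(0.78) = 78%, Φ(1.00) = 84%, Φ(1.36) = 91%

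These lie slightly above the simulated values, as the normal approximation should.

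**Step 4: type I error**

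Under rule (a) at 36 per arm, overall type I error is 4.3%, 4.0% and 3.5% at correlations 0.5, 0.6 and 0.7. Across all settings run it is about 3.5–4.7%, so it is not inflated.

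**The case against.** The strongest objection is that the selection rule is inferred. No section says that a p-value chooses the covariates or that a non-significant variable goes unadjusted. The adjustment sentence stands in the Discussion, and a covariate list is often left to a fuller document. That stands as a limit on the reading. It does not remove the point: the article ties adjustment to observed differences, names only tests for finding them, and credits the adjustment with a protection it cannot give. Nor does the sentence rest on adjustment alone, since it names randomisation first; so it needs rewording, not deletion.

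Several stronger readings are tempting, and the documents do not support them.

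- **The tests miss a 0.5-SD imbalance 35–45% of the time.** The arithmetic is right (35.0% at 45 per arm, 44.7% at 36), but it is the type II error for a true population difference, which randomisation makes zero. An observed 0.5-SD imbalance lies above both thresholds in step 1 and would be significant (p = 0.020 and p = 0.037).
- **The false-positive rate is inflated.** Overall it is below 5%. Among trials with a larger but non-significant imbalance (baseline |t| above 1.2, roughly 18% of trials), it is 8–10% at 36 per arm. That subset is picked for its imbalance and does not describe the procedure as a whole.
- **Baseline testing costs power.** A plain t-test has 55% power at 36 per arm, against 56–57% under the inferred rule. The shortfall is the gain forgone by not always including a prognostic covariate.
- **Table 3 tests baseline scores between arms.** It does so only for participant characteristics; the outcome rows list no between-group test at T-0. The wider reference to baseline data is in section 2.9.

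It is also fair to say that efficacy is only preliminary here. That limits the consequence, but the change costs almost nothing.

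**Conclusion.** The point holds in a limited form. The article plans uninformative baseline tests, makes adjustment depend on differences seen after randomisation, names no baseline covariate in the listed analyses, and credits the adjustment with part of the protection against selection bias. On the most natural reading, observed imbalances up to about 0.42 SD (0.47 SD if only 36 per arm are analysed) would count as balance.

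The consequence is lost precision. For a 0.5-SD effect and a covariate correlated 0.5–0.7 with the outcome, always adjusting would raise power by about 11 to 26 points at 36 per arm (from 56–57% to 67–83%), and by about 10 to 24 points at 45 (from 66–67% to 76–91%). At correlation 0.3 the gain is about 3 points. These sizes rest on assumed correlations, one normally distributed covariate, a 5% level for the baseline tests and the inferred selection rule. The case against baseline testing, and the misattributed protection, do not depend on those figures.

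**What to change.** 1. Remove the between-group tests of participant characteristics and baseline data from section 2.9, and those in the participant-characteristics row of Table 3. Report baseline by arm descriptively.
2. Replace adjustment for whatever differences appear with covariates fixed in advance on prognostic grounds and used whatever imbalance is observed. Include at least the T-0 value of the outcome where it is collected. Table 3 schedules one for depression, perceived support, intimate relationship, coping and self-efficacy, but not for post-abortion growth.
3. Name these covariates in the models of section 2.9 and Table 3, so that the Discussion and the listed analyses agree.
4. Reword the Discussion: randomisation and allocation concealment protect against selection bias, while adjustment improves precision and deals with chance imbalance.

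The cost is wording and an early decision on the covariate list. No further data or participants are needed, because T-0 measurement is already planned.

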## 4. Conclusions

This paper proposes a protocol of a clinical trial to assess the feasibility, acceptability, and potential effects of a comprehensive supportive intervention that was developed to address the psychological health of Chinese women undergoing an abortion. Results will be used to assist intervention refinement and direct a future full-powered trial. Practical experience will be gained throughout the clinical trial, which would also provide evidence for further implementation of the intervention.

## Figures and Tables

**Figure 1 ijerph-19-06611-f001:**
[figure not shown]
The Transactional Model of Stress and Coping.

**Figure 2 ijerph-19-06611-f002:**
[figure not shown]
SPIRIT standard flow diagram.

**Table 1 ijerph-19-06611-t001:** Intervention description according to TIDieR checklist.

TIDieR Item	Intervention Group	Control Group
**1.** **BRIEF NAME**	The START intervention	Standard abortion care
**2.** **WHY**	Based on the Transactional Model of Stress and Coping, the START intervention intends to help women cope with abortion experience by addressing the specific stressors they face in the Chinese context, hence promoting well-being	N/A
**3.** **WHAT-Materials**	Consultation, an information booklet, a WeChat-based public profile page, and a hotline	N/A
**4.** **WHAT-Procedure**	All participants allocated to the intervention group will be offered a 30-min face-to-face consultation. The consultation includes a brief introduction of the public profile page, Q&A, and offering emotional support and information on available coping resources. A printed information booklet will be provided during the consultation. Meanwhile, by scan the QR code, participants will be endowed with unlimited access to the public profile page till the closure of the project. A hotline will also be offered.	(1) prior abortion consultation on informed choice of pregnancy; (2) abortion preparation education on abortion practice, and steps involved; (3) a brief discharge education session on warning signs of potential complications and post-abortion contraception; and (4) a regular 2-week post-abortion appointment to determine the completion of the abortion.
**5.** **WHO PROVIDED**	The consultation, information booklet, and managing the public profile page will be carry out by the primary researcher who is a qualified abortion counsellor. Hotline will be answered by a registered nurse who has more than 10 years clinical experience in abortion care.	Prior abortion consultation and post-abortion exam-by doctors Abortion preparation and discharge education-by nurses
**6.** **HOW**	Consultation (face to face) Information booklet (hard copy) Public profile page (internet) Hotline (telephone)	Face to face
**7.** **WHERE**	Consultation (the consultation room) Information booklet (the consultation room) Public profile page (WeChat based) Hotline (telephone-base)	Health centre facilities
**8.** **WHEN and HOW MUCH**	Consultation (after women made their abortion appointment, 30 min) Information booklet (during the consultation, one copy to take home) Public profile page (from the consultation, unlimited access until the closure of the project) Hotline (from the consultation, available during workhours)	Prior abortion consultation—at women’s first appointment (10–20 min); Abortion preparation education—after women made their abortion appointment (5–10 min); post-abortion education—before women are discharged (10 min); The post-abortion exam—2 weeks after abortion
**9.** **TAILORING**	Participants in the intervention group will receive the same intervention	N/A
**10.** **MODIFI-CATION**	Cannot be reported until the study is complete	N/A
**11.** **HOW WELL**	The research nurse and reception nurses involved in the trial will be trained initially. A researcher logbook will be kept recording intervention delivery of each participant. Adherence to the intervention will be assessed by participants self-reported usage info collected during follow-ups	N/A
**12.** **ACTUAL**	Cannot be reported until the study is complete	N/A

Abbreviations: Q&A: questions and answers; N/A: not applicable.

**Table 2 ijerph-19-06611-t002:** Content of the information booklet and platform.

Categories	Themes	Example Items
Abortion	Facts about abortion	General information about abortion Pregnancy calculation and ectopic pregnancy Abortion practice in Beijing
	Different types of abortion	Medical abortion and steps involved Aspiration/surgical abortion and steps involved Features of aspiration abortion and medical abortion
	Q&A	What is your legal position, e.g., gestation age limits; no need for husbands’ or partners’ permission; and Nation ID required etc. How much does abortion cost? Does abortion hurt and what is a painless induced abortion? What will you experience during an abortion? How could you know your abortion is complete? Will an abortion cause infertility? How will you feel if you have an abortion
	Aftercare and follow-up examination	Follow-up examination and why it is necessary Symptoms requiring contacting your health provider, going to local emergency room, or calling 120 for Emergency Health Aid.
Intimate Relationship	A healthy relationship	Important characteristics of a healthy relationship Rights and responsibilities in a relationship Equality in intimate relationships
	Identify and deal with a dangerous relationship	Signals of unhealthy relationships Options for women experiencing an unhealthy/dangerous relationship Recognising Intimate Partner Violence (IPV) Options for women experiencing IPV
	About sex	Consent and your legal position Options for women who are forced to engage in a sexual activity
Available Coping Resources	Coping with abortion experience	Suggestions from experts (Chinese Health & Medical Development Foundation) Suggestions from women who have experienced an abortion
	Taking care your emotions	Talk to someone you trust: Tips on finding a reliable person to talk to (Marie Stopes China) Medication: free medication; Apps recommendation e.g., Tide Reading: e.g., Trauma and Recovery by Judith Herman _Chinese version Post-abortion counsellor
	Cope with IPV or sexual violence experience	Free social support services e.g., Beijing Women’s Federation hotline; The Maple Women’s Psychological Counselling Center hotlines etc. Self-help guides e.g., Guidelines for dealing with sexual assault (Marie Stopes China); SARSAS Suggestions from police Stories from IPV survivors

Abbreviations: ID: identification; IPV: intimate partner violence; Q&A: questions and answers; SARSAS: Self-help guide to rape and sexual abuse—Chinese version.

**Table 3 ijerph-19-06611-t003:** Data collection schedule and analysis method.

Concept (What)	Time (When)	Method (Who, Where, and How)	Measure (by What)	Method of Analysis
**Participant characteristics**	T-0	Primary researcher, at the clinic, face to face	Self-design questionnaire on sociodemographic characteristics, health history, and current gestation	Descriptive statistics X^2^ test comparing differences between groups of categorical/dichotomous variables *t*-test/Mann–Whitney U test comparing differences between groups of continuous variables
